##### Secondary

**PE of ETs against malaria infections (both with clinical symptoms and asymptomatic)**

A similar proportional hazard model used for analyzing the primary endpoint above will be applied. The malaria hazard ratio between ET and control will be estimated, along with 95% CI.

**PE of ETs against malaria infections (both with clinical symptoms and asymptomatic)**

A similar proportional hazard model used for analyzing the primary endpoint above will be applied. The malaria hazard ratio between ET and control will be estimated, along with 95% CI.

**PE analysis without baseline covariates**

A PE analysis of clinical malaria infection will be also performed by removing all the baseline covariates from the proportional hazards presented above and keeping the treatment arm as the only covariate in the proportional hazard model. The hazard ratio between ET and control will be provided, along with a 2-sided 95% CIs. A similar analysis will be performed for clinical and asymptomatic malaria infections combined.

**Anemia**

The first study on ET [14] suggests ET has a protective effect against anemia. In this study, an in-depth health examination of the recruited children for malaria follow-up will be conducted at the beginning and the end of the transmission season in both Year 1 and Year 2 to monitor severe anemia. A mixed-effects logistic regression will be used to compare ETs and control in the anemia proportion. The model has anemia status (Y or N) as the outcome; a similar set of covariates as in the proportional hazards model in the primary endpoint analysis is used, with two additional terms of time (baseline, Year 1, Year 2) and time-by-treatment interaction, along with random effects to count for correlations among the subjects within the same cluster and among multiple anemia episode within the same subject, used. The regression coefficient associated with treatment arm quantifies the ratio between the ET and control arms on the odds of getting anemia, which will be estimated, along with a 95% confidence interval.

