## Trial design {8}

The trial design is a 2-armed cluster randomized control trial (cRCT) with 17 clusters (villages) per arm for evaluating the protective efficacy of the SR intervention. Clusters are the unit of replication in this design, and they will be randomly allocated to one of the two arms. Both the replication and randomization in our design are essential to distinguish the effect of ETs from other village-level variation in malaria incidence.

Villages that have not participated in the previous SET cRCT, and villages that received standard pyrethroid-only LLINs (Permanet 2.0) from the National Malaria Control Program (NMCP) distribution campaign in May 2021 will be enrolled. We will exclude villages being treated by IRS and/or new generation bed net campaigns.

The control arm of this cRCT will include 17 villages with universal coverage of LLINs (defined as 1 LLIN for every 2 people) and no ETs. The 17 villages in the treatment arm will receive universal coverage of LLINs plus ETs. For those households assessed to not have met thresholds of universal coverage, topping up of LLINs will be conducted as needed.

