### Sample size {14}

The number of villages for the cRCT is estimated at 17 per treatment arm based on the power analysis which is detailed in the Statistical Analysis Plan.

The sample size determination on the required number of households per cluster for testing the primary hypothesis on PE is based on the hazard rate comparison in the proportional hazards regression model. With the following specifications: power = 80%, 2-sided type-I error rate = 5%.True PE/Minimum effect size = 35%Baseline first-time malaria infection hazard rate = 1.5 cases of falciparum malaria per person-year (conservative estimate based on control arm data from first SET cRCT)Coefficient of variation (k) = 40% (based on first SET cRCT)Loss to follow-up (LTFU) rate = 20%Monitoring = 2 years to capture 2 peak transmission seasonsOne interim analysis for efficacy and non-binding futility with the O’Brien-Fleming error spending function when 50% information is collected

With 17 clusters per treatment, 55 children (aged 0.5 to 10 years old) from 55 different households per cluster are expected to yield 1315 independent first-time malaria events with a 24-month follow-up period to yield 80% power in testing the primary hypothesis on PE. Since the sample size already factors in a 20% LTFU rate, there is no need for replacement subjects.

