### Statistical methods

#### Statistical methods for primary and secondary outcomes {20a}

The baseline characteristics of the enrolled subjects, households, and clusters will be summarized by treatment arm (control arm, LLIN and intervention arm, ET + LLIN). Specifically, we will examine subject age and gender at the individual level, wall type and roof type, house open eaves, number of windows, number of doors at the household levels, and cluster population and baseline prevalence rate at the cluster level.

In the following analysis that involves malaria incidence, a child will not be considered at risk for malaria for 2 weeks after any treatment for malaria.

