**Effect of ETs on malaria prevalence**

Malaria prevalence data will be collected at baseline and at the end of Year 1 and Year 2. A mixed-effects logistic regression as used in the anemia analysis above will be used to compare ETs and control on malaria prevalence over time, with the outcome anemia status being replaced malaria status (Y or N).

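### The anaemia and malaria-prevalence models make no allowance for village-level shifts between surveys, so their follow-up confidence intervals are too narrow if villages drift

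*Protocol article*

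**What the plan says.** The Anemia paragraph under Statistical methods {20a} sets out a mixed-effects logistic regression of anaemia status. Its fixed part has time at three levels (baseline, Year 1, Year 2), a time-by-treatment interaction, and baseline covariates, for which "a similar set of covariates as in the proportional hazards model in the primary endpoint analysis is used". Its random part is described as "along with random effects to count for correlations among the subjects within the same cluster and among multiple anemia episode within the same subject". The 95% interval is attached to the coefficient for treatment arm.

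The paragraph on malaria prevalence carries this model over: "A mixed-effects logistic regression as used in the anemia analysis above will be used to compare ETs and control on malaria prevalence over time". Its data come from baseline and the ends of Years 1 and 2.

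The opening of {20a} lists the baseline characteristics to be summarised by arm, among them "cluster population and baseline prevalence rate at the cluster level". The primary model takes those baseline covariates that are relevant, without naming them.

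**The concern.** In a model with baseline rows and a time-by-treatment term, the effect of the intervention is a comparison between arms of how villages changed. A constant village effect and a constant child effect both cancel from a change. What remains, as far as this model is concerned, is sampling noise between children. Any movement shared by all children in a village between two surveys has no term to absorb it.

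The article gives reasons to expect such movement. Transmission is seasonal. Baseline infection is measured just before every cohort child is cleared of parasites, so a village's baseline level need not persist to Year 1.

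Anaemia is the first secondary objective, parasitaemia is a listed secondary outcome, and the trial's findings go to the WHO advisory group. Intervals that are too narrow would make a chance difference in village trends look like an effect of the tubes, in either direction.

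A second, conditional problem arises in the prevalence analysis. If village baseline prevalence is one of the covariates carried over, the same baseline data sit both in the outcome rows and among the predictors. That shrinks the estimated village variance.

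**Working it through.** **Figures in the plan.** The article states no error rate, variance component or prevalence for these two models. The nearest figure is the primary sizing: "55 children (aged 0.5 to 10 years old) from 55 different households per cluster are expected to yield 1315 independent first-time malaria events", with "power = 80%, 2-sided type-I error rate = 5"%, "True PE/Minimum effect size = 35"%, a control rate of 1.5 per person-year, a between-cluster coefficient of variation of 40% and 20% loss. It reproduces:

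- Children retained: 34 × 55 × 0.8 = 1496, or 44 per village.
- Exponential times over two years: control 1 − exp(−3.0) = 0.950; EaveTubes 1 − exp(−1.95) = 0.858; mean 0.904; 1496 × 0.904 ≈ 1352 events.
- With gamma frailty (CV 0.4) the count is about 1294. The stated 1315 lies between.

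**Inputs for this check.**

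- From the article: 17 villages per arm ("The trial design is a 2-armed cluster randomized control trial (cRCT) with 17 clusters (villages) per arm"), three time levels, 44 children per village after loss.
- Assumed: 40% or 50% malaria prevalence, 20–25% anaemia, 25 or 26 under-fives per village, and village-by-survey SD τ on the logit scale.

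**Formula.** With m children and prevalence p, a village's change in log odds has sampling variance of about 2(1 − ρ)/(m p(1 − p)), where ρ is the within-child correlation. Drift adds 2τ². Ignoring drift understates the variance by the factor

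VIF = 1 + τ² m p(1 − p)/(1 − ρ), and the true error is 2[1 − Φ(1.96/√VIF)].

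Example, prevalence with p = 0.4, m = 44, τ = 0.3, ρ = 0: VIF = 1 + 0.09 × 44 × 0.24 = 1.95, and the error is 2[1 − Φ(1.40)] ≈ 16%. Anaemia with p = 0.2, m = 26, τ = 0.3: VIF = 1 + 0.09 × 26 × 0.16 = 1.37, error about 9.5%.

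**Simulation of the model with village and child effects** (no true effect, 1000 runs per row). The simulated columns give the error of the two treatment-by-year terms; the joint column tests both together.

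| τ | Prevalence, formula | Prevalence, simulated | Prevalence, joint | Anaemia, formula | Anaemia, simulated |
|---|---|---|---|---|---|
| 0 | 5.0% | 3.5–4.1% | 2.8% | 5.0% | 3.1–3.2% |
| 0.2 | 10.0% | 6.4–7.0% | 7.6% | 7.0% | 3.9–5.1% |
| 0.3 | 16.0% | 11.2–11.3% | 14.6% | 9.5% | 5.7–6.5% |
| 0.4 | 23.2% | 16.1–16.4% | 22.7% | 12.9% | 9.1–9.8% |

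The fit is slightly conservative at τ = 0, so these simulated values are a little low.

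**Remedy tested at τ = 0.3.** Adding a village-by-survey effect gives 5.4–6.0% for prevalence (joint 5.9%) and 4.1–5.2% for anaemia.

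**Simulation with a village intercept only** (50% prevalence with 44 children; 25% anaemia with 25 children). Village SD was 0.4–0.6 and between-survey correlation 0.8–0.5, so τ runs from 0.4√0.2 = 0.18 to 0.6√0.5 = 0.42.

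- Two sets of 400 runs per setting gave 9–22% and 11–29% for the prevalence interaction, and 8–19% and 5–16% for anaemia. Separate runs of the same kind of model gave 12–24% and 6–13%.
- The single highest value for each outcome (29% and 19%) was not reached in the other sets, so the summary ranges do not use it.
- In the same simulated data, a village-level follow-up comparison adjusted for baseline (34 − 3 = 31 df) gave 6–7%.
- Year 1 prevalence contrast between arms: about 7–13% without village baseline prevalence as a covariate, and 14–22% with it.

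**The case against.** The strongest reply is that a separate analysis plan exists, that the article describes the random effects in general words, and that it does not exclude a village-by-survey term. That is true, and such a plan may specify more. But the article does more than stay silent: it states which two correlations the random effects are there to handle. A plan that followed that wording would have the fault.

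Four stronger readings are tempting, and the documents do not support them.

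- A reader might infer that the true error is some fixed multiple of 5%. The article gives no village-by-survey variance, no prevalence for either outcome and no number of under-fives. Its 40% coefficient of variation concerns malaria incidence between clusters and says nothing about drift. Carried to the logit scale, with 5–50% of village variance assumed to be drift, it gives about 5–18% for anaemia and 7–40% for prevalence by the formula. At small drift, anaemia shows little or no inflation.
- A reader might infer that the anaemia interval the article names is itself badly wrong. That interval belongs to the treatment-arm coefficient, whose error was about 4–6% with village and child effects fitted. One village-only set gave 8–13% for prevalence, so the evidence conflicts and nothing is claimed. With baseline as reference that coefficient is the pre-intervention contrast, which is a separate matter. The effect after intervention has to come from the interaction or a follow-up contrast.
- A reader might take it as settled that baseline prevalence enters the prevalence model. It is listed as a characteristic to summarise, and only relevant covariates are carried over. Its inclusion is a fair reading, not a certainty.
- A reader might say the plan's stated 5% is breached. That rate is stated for the primary hypothesis. For these outcomes 5% is only the nominal level implied by a 95% interval.

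One limit of the check also stands. The simulation uses the model's three time levels, whereas the Outcomes section lists four anaemia measurements.

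**Conclusion.** The point holds conditionally. As worded, both models treat village levels as constant across surveys. If they are not, the intervals for time-by-treatment and for follow-up arm contrasts are too narrow. At assumed logit-scale drift of about 0.2–0.4 the error is roughly 6–24% for prevalence and 4–16% for anaemia, against a nominal 5%; at zero drift there is no inflation. These ranges rest on the assumed prevalences, numbers measured and drift listed above, none of which the article supplies apart from the 44 retained children. The doubled use of baseline prevalence matters only if that covariate is carried over. The primary test is unaffected. The change is worth making because it is cheap and the effect on prevalence is material at moderate drift.

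**What to change.** In both the Anemia and the malaria-prevalence paragraphs, do one of the following:

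- Add a village-by-survey random effect to the village and child effects, and refer the treatment contrasts to a small-sample distribution with about 34 − 2 = 32 degrees of freedom.
- Drop the baseline rows from the outcome, use baseline as a covariate only, and estimate the arm contrast at each follow-up survey with a village random effect.

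In the prevalence model, if village baseline prevalence is among the covariates, do not keep it while baseline status is also an outcome row.

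The cost is a sentence of plan wording and one model term, or a reshaped dataset. The intervals for two secondary outcomes become wider. No new data are needed and the primary analysis does not change.

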**Effect of ETs on malaria prevalence**

Malaria prevalence data will be collected at baseline and at the end of Year 1 and Year 2. A mixed-effects logistic regression as used in the anemia analysis above will be used to compare ETs and control on malaria prevalence over time, with the outcome anemia status being replaced malaria status (Y or N).

**Incidence rate**

The malaria incidence rate is defined as the ratio of the number of new malaria cases during the follow-up period vs the sum of the time at risk (in year) across the individuals within the same cluster. The incidence rates per person-year during the whole intervention follow-up will be calculated by cluster in the ET and the control arms respectively. Summary statistics of the cluster-level incidence rate will be provided by treatment arm; the incidence ratio between the two arms will be also calculated.

**Analysis of the relationship between malaria hazard rate and entomological endpoints**

To explore the relationship between the malaria hazard rate and the entomological endpoints, a similar model as the proportional hazards regression model used to address the primary objective on the malaria infection will be applied to the clusters from which the entomological data are collected, with similar random effects specification. For the covariates in the model, in addition to those used for analyzing the primary endpoint, we will also include a covariate that captures the entomological information; whether it is a linear or non-linear term will be informed by the exploratory data analysis of the relationship between the cluster-level incidence rate and each of the entomological endpoints (e.g., indoor mosquito density and sporozoite positivity rate if there is enough data). The regression coefficient associated with the entomological covariate quantifies how the entomological covariate affects the malaria hazard rate.

**Safety assessment**

Mean, minimum and maximum frequency, and percentage of AEs and SAEs across clusters among enrolled subjects will be summarized by treatment arm. The AE/SAEs summary will be provided for both clinical diagnosis and symptoms. In addition, they will be labeled as Probable, Possible, Plausible (such as dermal events, oral events, Inhalation events), or Unlikely (eye Irritation, headache) due to ETs.

#### Interim analyses {21b}

A formal interim analysis during the intervention period will be conducted to test the primary hypothesis as outlined above. The interim analysis will be performed by an independent statistician on the DSMB, and the interim outcome report will be shared only with In2Care and VCAG, not with UND or Cote d’Ivoire investigators to mitigate unintentional bias in data collection in the remaining period of the study after the interim analysis. The final decision to stop should always rest with the DSMC, not the investigators, or the funder.

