**Discussion:**

Findings will serve as an efficacy trial of ETs and will be submitted to the WHO Vector Control Advisory Group (VCAG) for assessment of public health value. Entomological outcomes will also be measured as proxies of malaria transmission to help develop guidelines for the evaluation of future In2Care® ETs products.

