### Oversight and monitoring

#### Composition of the coordinating center and trial steering committee {5d}

In2Care will serve as the lead organization for this program and will assume the overall responsibility for management, oversight, and administration for the program. The coordinating personnel at UND will include the Lead PI, Co-Investigators, Program Manager, and Finance Manager. UND will communicate on a day-to-day basis with In2Care and VCPEC-IPR. VCPEC-IPR will be responsible for running the cRCT on a day-to-day basis which includes but will not be limited to conducting a baseline survey, deploying ETs, entomological monitoring, and subject follow-up. Representatives from VCPEC-IPR and UND will all serve on the data management team to oversee the development and implementation of data collection, recording, and cleaning.

A Trial Steering Committee (TSC) will be established. Members on the committee will have the clinical, epidemiological, and statistical expertise to monitor study progress and safety of participants, and the committee will have access to the study data. SOPs will be developed, adhering to Good Clinical Practice and Good Field Entomology Practice.

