#### Composition of the data monitoring committee, its role, and reporting structure {21a}

The trial will not consist of a data monitoring committee as the TSC will serve in this capacity. In addition, routine data monitoring and management for Quality Assurance and Quality Control will be conducted in partnership between UND and VCPEC-IPR data management teams.

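### The interim section names a monitoring board that the protocol rules out, and sends the directional interim report to the organization that leads the trial

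*Protocol article*

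**What the plan says.** Interim analyses {21b} makes four statements:

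- On who does the work: "The interim analysis will be performed by an independent statistician on the DSMB".
- On who sees the result: "the interim outcome report will be shared only with In2Care and VCAG". The university and the Côte d'Ivoire investigators are shut out.
- On why they are shut out: "to mitigate unintentional bias in data collection in the remaining period of the study after the interim analysis".
- On who decides: "The final decision to stop should always rest with the DSMC, not the investigators, or the funder".

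The section on the data monitoring committee {21a} says: "The trial will not consist of a data monitoring committee as the TSC will serve in this capacity". Adverse event reporting and harms {22} also places safety oversight with the TSC.

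The section on the coordinating center and TSC {5d} says: "In2Care will serve as the lead organization for this program and will assume the overall responsibility for management, oversight, and administration". It adds that the university team is in daily contact with In2Care and with the field institute, and that the TSC can see study data. It does not say which TSC members, if any, are independent of In2Care.

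**The concern.** Two things do not fit together. The paragraph that governs early stopping relies on a board, under two names, that another section says will not be formed. And the party that receives the interim result is the one in overall charge of the trial, while the teams it works with daily are kept from that result for fear of bias.

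The trial cannot be fully blinded, as {17a} acknowledges. Under {18a}, a child is tested when there is fever, recent fever or a parent's report of illness, and under {11a} and {11c} the tubes are inspected and repaired throughout follow-up. Knowledge of the interim direction could affect how hard these activities are pursued and what villages and staff are told. The primary analysis text under {20a} leaves discretion at both boundaries: the trial may go on after crossing either one. It therefore matters who holds the information on which that discretion is used. A disclosure of interim results cannot be reversed.

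**Working it through.** No calculation settles this point. It turns on the texts set side by side, with one calculation to size the exposure.

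1. **Who decides.** {21b} names a DSMC and places the statistician on a DSMB. {21a} says no data monitoring committee will be formed and gives its role to the TSC. No section sets up a DSMB or DSMC. The TSC is therefore the only body that could decide, but {21b} does not name it. The statistician's independence is defined only through the excluded board.

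2. **Who receives the report.** {21b} names In2Care and VCAG, with the word 'only'. The TSC is not named.

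3. **What the report must show.** Under {20a} the interim z-score of the log hazard ratio (ET against control) is compared with −2.7965 for efficacy, −0.7288 for futility and +2.7965 for harm. These bounds cannot be applied without knowing the sign. The A/B arm labels in {17a} would not hide the direction from anyone told which bound was met. {17b} allows unblinding only after data lock and makes no exception for the interim look, so it needs reconciling too.

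4. **Whether the firewall works.** The report is withheld from investigators to limit bias in later data collection, yet it goes to the organization that manages the trial and speaks with one of the excluded teams every day. The stated reason for withholding applies to that organization as well.

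5. **How long the exposure lasts.**
 - Trigger: 0.5 × 1315 = 657.5, rounded up to 658. This reproduces the protocol's figure.
 - Protocol timing: the look falls around the end of Year 1, so 24 − 12 = 12 months remain.
 - Timing from the planning inputs in {14}: 17 × 55 = 935 children per arm, a control rate of 1.5 per person-year, and 35% efficacy, giving 1.5 × 0.65 = 0.975 under ET. With m children per arm contributing, expected first events by t years are m × [2 − exp(−1.5t) − exp(−0.975t)].
 - m = 935 (no loss): 935 × (2 − 0.5881 − 0.7082) = 658 at t = 0.354 years, or 4.2 months.
 - m = 0.8 × 935 = 748 (20% contribute nothing): 748 × (2 − 0.4907 − 0.6296) = 658 at t = 0.475 years, or 5.7 months.
 - The second case with a gamma between-cluster CV of 40%, where exp(−x) becomes (1 + 0.16x)^(−1/0.16), gives 6.0 months.
 - Remaining follow-up: 24 − 6.0 = 18.0 to 24 − 4.2 = 19.8 months.

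The range is therefore 12 months on the protocol's statement and 18 to about 20 months on its planning rates. The latter assume constant hazards, a simultaneous start and first events only.

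**The case against.** The strongest reply is that the role is not vacant. The TSC takes it under {21a}, has clinical, epidemiological and statistical expertise and data access under {5d}, and oversees safety under {22}. Because the analyst sits on the board, 'shared only with' may simply govern release beyond that board. This stands. A reader might infer that nobody can make the stopping decision, that the rule keeping it from the funder is empty, or that the deciding body is barred from the result. The documents do not support these readings: if the TSC acts as the committee, it can decide on its own data access. An article may also leave TSC membership to a charter, so the silence on independence is not a defect in itself. It matters here because the rest of the arrangement depends on it.

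The reply on bias is partly right. Visit schedules are fixed, insert replacement follows a 70% bioassay threshold, laboratory work is blinded, and the field institute, not In2Care, runs the trial from day to day. Any influence would be indirect. It is not excluded, because case finding and repairs still depend on people in regular contact with the lead organization.

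Two labels need care. Calling In2Care the manufacturer or funder is inference: the product carries its brand ("help develop guidelines for the evaluation of future In2Care® ETs products"), but the role stated is lead organization. That the report is unblinded is also inferred, from the directional stopping rule. For VCAG, the documents give it no part in trial conduct, so the case for withholding results from it is weaker and rests on its later assessment of the product.

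**Conclusion.** The point holds as a contradiction between {21b} and {21a}, together with a distribution list that undermines the protocol's own safeguard. As written, directional interim results would reach the organization in overall charge of an incompletely blinded trial with about 12 of 24 months of follow-up left, or 18 to about 20 if events accrue at the planning rates. This rests on two readings: that a report serving this stopping rule reveals direction, and that 'only' means what it says.

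A reader might go further and infer that In2Care would in effect know the final result. The documents do not support that. At the stated 50% information, the interim and final z-scores correlate at √0.5 = 0.71, and the final z given the interim z has a standard deviation of √(1 − 0.5) = 0.71, so a mid-range interim result leaves the outcome open. A closer link would require assumptions about between-cluster variation that the protocol does not fix. The point needs no such figure.

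**What to change.** Reconcile {21b} with {5d}, {21a} and {22} before any interim data are opened:

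- Replace DSMB and DSMC with one named body: the TSC members who are independent of the lead organization, the university team and the field institute, working with the independent statistician.
- State that this body receives the interim results and makes the stopping decision.
- Give the lead organization and the investigators, and preferably VCAG, only 'continue' or 'stop' until database lock.
- Add to {17b} the exception that the interim look requires.

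Even 'continue' carries some information, since it suggests a z-score between the bounds. The non-binding futility rule weakens that inference, and it is far less than a full report.

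The cost is protocol and charter wording, plus confirming that the TSC has independent members and that the statistician's appointment does not depend on a board that will not be formed. If no TSC member is independent, some would have to be added. Sample size, boundaries and data collection are unaffected.
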